## Study outcomes and data collection procedures

### Outcomes

The primary study outcomes are total circulating and fecal BAs, taurine-conjugated BAs, and DCA. Secondary outcomes include body weight, body composition, dietary change (i.e., MedDiet adherence), physical activity (i.e., steps per day), metabolic risk, circulating cytokines (e.g., IL-6, TNFα), gut microbial community structure and composition, fecal short chain fatty acids (SCFAs) (i.e., butyrate, acetate, propionate), and exfoliated intestinal cell gene expression levels. Data collection will take place at UIC and by telephone at baseline, month 3, and study end. All data collection staff will be trained and certified in informed consent, testing procedures, specimen processing, and data management. All procedures will be written and stored electronically. Major changes to study design will first be reviewed and approved by the IRB before implementation. The primary data collectors and lab technicians will be blinded to randomization group assignment by having the assignment hidden from view in their individual REDCap account.

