## Statistical analysis plan

### Sample size

We calculated the sample size to detect group differences in three circulating and fecal BA outcomes (total BAs, taurine-conjugated BAs, and DCA) using results reported by Biemann et al. [19] and Aleman et al. [18] as a guide. In Biemann et al. [19], data were summarized as medians, interquartile ranges, and sample sizes; we estimated the corresponding means and standard deviations [62]. Estimated effect sizes for diet intervention on serum total BAs and taurine-conjugated BAs are 0.75 and 1.2 (assuming the correlation coefficient between pre and post measurements is 0.9 as commonly observed in repeated assays). Estimated effect size on fecal DCA is 0.67 using the raw data provided by Aleman (assuming change in the control group is 0) [18, 62]. For each dependent variable, the overall level of type I error is set at *α* = 0.05; that is, no adjustment is made for correlation among dependent variables and hence tests of these variables are not independent. The sets of variables examined in Hypotheses 1 and 2 should be interpreted as related. With 4 groups, there are 6 pairwise contrasts among cell means at a given occasion; we plan to test 3 of these using *t*-tests at the Bonferroni-adjusted *α*^′^ = 0.05/3 ≈ 0.017 significance level. For the smallest effect size 0.67, we need 41 subjects per group to afford power of 0.80 at *α*^′^ = 0.017. Note that in all cases these are one-sided tests of superiority in that change in one group’s mean is hypothesized to be greater than change in that of another group [63, 64]. For the smallest effect size, we need 164 subjects to complete the study, which offers ample power for the other effect sizes. Assuming 15% dropout at 6 months based on our previous studies, the recruitment target is 192 subjects (48 per arm).

Normal continuous variables will be presented as mean ± standard deviation. Continuous variables which cannot be transformed to achieve normality will be presented as median (interquartile range). Discrete variables will be presented as percentages.

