Statistical analysis will be conducted using SAS v9.4 (Cary, NC). Independent and dependent *t*-tests will be employed to investigate differences in outcome measures between and within study groups, respectively. Any non-normal variables which cannot be transformed will be analyzed with the Mann-Whitney *U* and Wilcoxon signed-rank tests. The effect of the interventions on change in primary outcomes at mid- and post-intervention will be examined using repeated-measures linear models with restricted maximum likelihood estimation and a fully specified covariance matrix in SAS [65–67]. Such modeling can handle missing data as long as the data is missing at random, making this method ideal for our intention-to-treat analysis. Baseline covariates including the stratification variables for randomization will be adjusted for in all models. We will determine Spearman’s rank correlations between changes in circulating and fecal BAs and changes in fasting glucose, insulin, HOMA-IR, and circulating pro-inflammatory cytokines. We will also determine partial correlations for the above by adjusting for pertinent covariates, such as BMI.

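### The model that handles missing data is assigned to the bile-acid primaries only; for weight and the other clinical, inflammatory, dietary and activity secondaries the only stated between-arm test is an unadjusted observed-case test

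*Protocol article*

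**What the plan says.** The analysis paragraph follows the sample-size text in the Statistical analysis plan of the Protocol article. It sets out two tiers.

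- **General tier.** Independent and dependent t-tests "will be employed to investigate differences in outcome measures between and within study groups". If normality fails: "Any non-normal variables which cannot be transformed will be analyzed with the Mann-Whitney" and Wilcoxon signed-rank tests.
- **Model tier.** "The effect of the interventions on change in primary outcomes at mid- and post-intervention will be examined using repeated-measures linear models", fitted by restricted maximum likelihood with a fully specified covariance matrix. The next sentence gives the reason: "Such modeling can handle missing data as long as the data is missing at random, making this method ideal for our intention-to-treat analysis". Then: "Baseline covariates including the stratification variables for randomization will be adjusted for in all models".

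The Outcomes section settles which variables fall in the model tier: "The primary study outcomes are total circulating and fecal BAs, taurine-conjugated BAs, and DCA". Weight does not: "Secondary outcomes include body weight, body composition, dietary change (i.e., MedDiet adherence), physical activity (i.e., steps per day), metabolic risk", followed by cytokines and the microbial, SCFA and gene-expression outcomes. The microbiome, qPCR/SCFA and gene-expression data have their own analysis sections and are outside this point.

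On attrition, the sample-size text says "Assuming 15% dropout at 6 months based on our previous studies", giving a target of 192 (48 per arm). Table 2 lists weight, hs-CRP, cytokines, glucose, insulin, HbA1c, HOMA-IR, ASA24 and MEPA-III at baseline, month 3 and month 6. DXA, blood pressure, the FFQ and steps are listed at baseline and month 6 only.

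**The concern.** The article does more than leave the secondary analysis open. It names a method for outcome measures in general, names a better one, and limits the better one to the primaries. Followed as written, the between-arm effect on weight is a two-sample test on people who have a month-6 value. That sits badly with the stated intention-to-treat aim. It also bypasses the stratification adjustment, which is promised for models and which a t-test cannot carry.

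Weight is secondary but not incidental. The Discussion says the design can separate the contributions of weight loss and dietary change. The calorie recommendations aim for about 5% loss in WL-A and WL-Med and weight maintenance in Med-A. How far the arms actually separated on weight is the evidence that the contrast was delivered. If bile acids are estimated by likelihood from everyone with data and weight from completers only, the two results describe different sets of people.

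**Working it through.** **1. The plan's own figures.** Inputs: effect size 0.67, one-sided α′ = 0.05/3, power 0.80. An exact t calculation gives 41 per group (power 0.806), so 4 × 41 = 164 completers, as stated. For dropout, 164/0.85 = 192.9 against the stated 192, and 1 − 164/192 = 14.6%. The sample size is not in dispute.

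**2. Who leaves a month-6 t-test.** 192 × 0.15 = 28.8, and 192 − 164 = 28. So about 28 to 29 participants have no month-6 value, and about 48 × 0.85 = 40.8 per arm remain.

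**3. What could be recovered.** For outcomes with a month-3 measurement, someone who leaves after month 3 still informs a repeated-measures model; a month-6 t-test discards that value. For DXA, blood pressure, FFQ and steps, a dropout contributes baseline only. Adjustment there mainly gains precision.

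**4. Simple bound on the weight bias.** All-randomised mean = 0.85 × completer mean + 0.15 × dropout mean. Suppose completers lose 5%. The dropouts' loss is an assumption.

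| Dropouts' mean loss | All-randomised mean | Overstatement by completers |
|---|---|---|
| 0% | 4.25% | 0.75 points |
| 1% | 4.40% | 0.60 |
| 2.5% | 4.63% | 0.37 |
| 5% | 5.00% | 0 |

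**5. Bias when dropout follows month-3 response.** From the documents: 48 per arm, 15% dropout, about 5% target loss. Assumed: no mean change in TDC; month-3 mean −3% in the weight-loss arm; SDs 3 (month 3) and 5 (month 6); month-3 to month-6 correlation ρ; random dropout in TDC; log-odds of dropout in the weight-loss arm rising by k per SD of poorer month-3 loss, with overall dropout held at 15%.

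Bias in the completers' difference = ρ × 5 × (mean standardised month-3 change among completers). That mean is −0.072, −0.132 and −0.203 for k = 0.5, 1 and 2. For example, 0.8 × 5 × (−0.203) = −0.81.

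| | k = 0 | k = 0.5 | k = 1 | k = 2 |
|---|---|---|---|---|
| ρ = 0.6 | 0 | −0.22 | −0.40 | −0.61 |
| ρ = 0.8 | 0 | −0.29 | −0.53 | −0.81 |
| ρ = 0.9 | 0 | −0.32 | −0.59 | −0.91 |

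Simulation (3,000 trials per cell) agrees. At ρ = 0.8 and k = 2 the completers' difference averaged −5.86 against a true −5.0. An estimate using month-3 values stayed between −4.99 and −5.06 in every cell. The standard error is about √(2 × 25/41) = 1.10, so the bias runs from about 0.2 to 0.8 of a standard error. The correction works here because dropout depends on an observed month-3 value. If it depended on later, unobserved weight, the model would not be guaranteed to remove the bias.

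**The case against.** The strongest reply is that this is a condensed article. The t-test sentence is general and covers the primaries too, nothing says t-tests are the sole or confirmatory analysis of weight, and a full analysis plan may extend the model. It stands this far: a reader might infer that the secondary outcomes are committed to t-tests alone, and no sentence says so. It does not remove the point, because the article states the model's scope as the primaries and names no other between-arm method for these outcomes.

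A second reply concerns consequences. A reader might infer that the trial's main conclusion rests on a completers' weight estimate, or that bile-acid effects would be credited to more weight loss than occurred. The documents support neither. The primaries and the sample size are bile acids, which the model covers. The planned correlations pair bile-acid changes with glucose, insulin, HOMA-IR and cytokines, not with weight change, and no mediation analysis on weight is described.

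Third, the Adherence section has weight recorded weekly in WL-A and WL-Med and monthly in Med-A, so some weights exist for people who later leave. That is fair. But no effect analysis is assigned to those weights, and no such regular schedule is stated for TDC. The per-protocol and antibiotic-exclusion analyses in the Discussion do not help, since both remove participants.

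Fourth, the size of the bias depends on an assumed dropout mechanism in one arm. That is correct and limits the claim to a range that includes zero.

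**Conclusion.** The point holds in limited form. As written, the only method described as handling missing data is confined to the bile-acid primaries. Between-arm effects on weight, metabolic markers, cytokines, diet scores, DXA, blood pressure and steps have only unadjusted observed-case tests. At the planned dropout these lose about 28 to 29 of 192 participants at month 6.

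The loss of participants and of usable month-3 values follows from the documents' own figures. The bias does not: the documents say nothing on whether dropout relates to response. Under the stated assumptions it is roughly 0.2 to 0.9 points on a 5-point weight difference; it is nil if dropout is unrelated to response. Even at the upper end it is below one standard error, and the sign of the weight difference would not change.

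The primary bile-acid conclusion is unaffected. What is affected is the estimate of how far the arms separated on weight, and the other secondary effects. The change is worth making because the better model is already planned and most of the data it needs are already scheduled.

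**What to change.** In the REML sentence, widen the scope from primary outcomes to primary and continuous secondary outcomes. Then:

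- Fit the same repeated-measures model, with the stratification factors, to secondary outcomes measured at baseline, month 3 and month 6: weight, glucose, insulin, HbA1c, HOMA-IR, cytokines, CRP, the ASA24 diet score and MEPA-III. For MEPA-III, first confirm which arms complete it: Table 2 shows no arm restriction, while the Dietary intake section describes its use at each time point for Med-A and WL-Med.
- For outcomes measured only at baseline and month 6 (DXA, blood pressure, FFQ score, steps), use a model adjusted for baseline and the stratification factors. The gain is mainly precision, and the text should not present it as recovering dropouts.
- Label the t-tests and rank tests descriptive.

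The cost is one changed sentence, a short addition and a few more model runs. No new visits or measurements are needed.

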### Randomization

The data manager, who has no contact with participants, will use the REDCap randomization module to randomly assign participants to (1) Med-A, (2) WL-A, (3) WL-Med, or (4) TDC, in a 1:1:1:1 allocation ratio. Stratified block randomization will be adopted to ensure good balance among the four study groups with respect to the selected covariates: sex, age (45–60 or 61–75 years), and baseline BMI (30–39.99 or 40–50 kg/m^2^). The randomization allocation will be created in SAS and imported into the REDCap randomization module.

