### Statistical analysis of the 16S rRNA data and predicted microbial metabolic pathways

ASV counts will be normalized using cumulative sum scaling [68]. Differences in community richness, evenness, and structure [alpha (i.e., Shannon index) and beta diversity (i.e., Unifrac [69] and Bray-Curtis distances)] between groups will be determined using PERMANOVA from vegan R package. Generalized linear mixed models (GLMMs) will determine the phenotypic variables, cardiometabolic outcomes, and BA-associated variables associated with each microbial ASV and genus level as implemented in MasLin [70], with treatment group as the main fixed factor, adjusting for important covariates, such as age and medication usage. Multiple comparisons will be adjusted using false discovery rate (FDR) [71]. An FDR-corrected *p*-value ≤ 0.001 will be deemed significant. All analyses will be done with R using functions encoded in the phyloseq package [72]. ASVs will be employed to determine the most likely associated microbial genes that encode for enzymes and associated microbial metabolic pathways using PiCRUSt2 [45]. GLMMs will be employed to determine the genes and metabolic pathways associated with each intervention arm with MasLin [70]. Finally, we will determine the likelihood that the ensemble of microbial genes associated with the production and consumption of DCA and H_2_S are affected by the interventions.

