### sCCA data integration

To assess the interdependencies among fecal microbiome, BAs, SCFAs, and host intestinal physiology in the intervention arms, we will deploy sparse Canonical Correlation Analysis (sCCA) [74, 83]. The groups of host genes, microbial ASVs, and microbial metabolites (i.e., SCFAs, DCA) identified by the 3-way sCCA will indicate potential biomarker sets for the participants in each one of the three intervention arms. We will also compare the 3-way correlative structures detected in each one of those groups to the others to elucidate the effects of the dietary interventions on the interactions between the host microbiota and the human gut relevant to CRC prevention and progression.

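### The planned correlations between bile acid changes and marker changes do not name randomised arm, so a pooled analysis can show an association that is absent within arms

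*Protocol article*

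**What the plan says.** The passage is in the statistical analysis plan of the protocol article, in the text that follows the sample size paragraph. After the repeated-measures models for the primary outcomes, the article plans Spearman "rank correlations between changes in circulating and fecal BAs and changes in fasting glucose, insulin, HOMA-IR, and circulating pro-inflammatory cytokines". The next sentence reads "We will also determine partial correlations for the above by adjusting for pertinent covariates, such as BMI". Neither sentence mentions randomised arm, and neither says whether the four groups are combined or handled separately.

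Just before them stands "Baseline covariates including the stratification variables for randomization will be adjusted for in all models". The Randomization section lists those stratification variables as sex, age group and baseline BMI group, so this sentence does not bring arm in either.

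Elsewhere arm is handled explicitly. The microbiome models are fitted "with treatment group as the main fixed factor, adjusting for important covariates, such as age and medication usage", and the sCCA section says "We will also compare the 3-way correlative structures detected in each one of those groups to the others".

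**The concern.** Arm is assigned at random and is intended to move the bile acids. Metabolic risk and circulating cytokines are secondary outcomes of the same interventions. Where an intervention moves both, arm is a common cause of the two changes. A correlation computed over all participants then mixes two things: whether people with a larger bile acid change also have a larger marker change, and whether both variables moved in the active arms. The second is already answered by the arm comparisons. Only the first bears on a link between bile acids and metabolic or inflammatory change.

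The mixing is greatest when the interventions work, which is also when these correlations would most readily be cited in support of the proposed mechanism.

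**Working it through.** **Inputs from the article.** Four arms, "in a 1:1:1:1 allocation ratio". Sample size section: "For the smallest effect size 0.67, we need 41 subjects per group to afford power of 0.80 at" the one-sided Bonferroni level 0.05/3; planning effects on bile acids of 0.67, 0.75 and 1.2; 164 completers; 15% dropout; 192 recruited.

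**The plan's own figure.** No figure is stated for the correlations, so the sample size is the one to reproduce. The normal approximation gives n = 2 × [(2.128 + 0.842)/0.67]² = 39.3, so 40 per group. The one-sided t-test gives 40.4, so 41, with power 0.806 at 41. Completers: 4 × 41 = 164. Recruitment: 164/0.85 = 192.9, against 192 stated. The figures reproduce, and N = 164 is used below.

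**Assumptions not in the article.** Effects on glucose, insulin, HOMA-IR and cytokines, varied here from 0.3 to 1.34 SD; normal changes with SD 1 in every arm; zero correlation within every arm; two-sided 5% tests of each correlation; BMI taken as a baseline value unrelated to arm.

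**Formula.** With equal arms, let a and b be the arm means of the two changes. Pooled over arms,

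r = cov(a, b) / √[(1 + var a)(1 + var b)].

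For the same shift d in three of four arms, var = d² × (3/4) × (1/4) = 0.1875d², so r = 0.1875d² / (1 + 0.1875d²).

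- 0.3 SD in both: 0.0169/1.0169 = 0.017.
- 0.67 SD in both: 0.0842/1.0842 = 0.078.
- Bile acids 1.2, marker 0.67: cov = 0.1875 × 1.2 × 0.67 = 0.1508; r = 0.1508/√(1.270 × 1.0842) = 0.128.
- Additive, arm means 0, 0.67, 0.67, 1.34 in both: var = 2 × 0.67²/4 = 0.2245; r = 0.2245/1.2245 = 0.183.
- Bile acids respond only to the diet, marker only to weight loss, 0.67 each: the products of the deviations cancel, so r = 0.

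**Simulation.** 10,000 trials per scenario with 4 × 41 completers and true within-arm correlation zero. The last three columns are rejection rates at nominal 5%.

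| Shifts against control | Mean pooled Spearman | Pooled | Partial on baseline BMI | Adjusted for arm |
|---|---|---|---|---|
| 0.3 in both, all active arms | 0.016 | 5.4% | 5.4% | 4.9% |
| Bile acids diet only, marker weight loss only | 0.000 | 5.0% | 5.0% | 5.0% |
| Bile acids 0.75, marker 0.3 | 0.038 | 7.9% | 8.0% | 5.1% |
| Bile acids 0.67 in all active arms, marker 0.67 in weight-loss arms only | 0.051 | 10.1% | 10.0% | 4.7% |
| 0.67 in both, all active arms | 0.076 | 15.9% | 16.2% | 5.0% |
| Bile acids 1.2, marker 0.67 | 0.122 | 34.7% | 34.5% | 4.8% |
| 0.75/0.75/1.2 in both | 0.153 | 50.3% | 50.1% | 5.4% |
| Additive 0.67/0.67/1.34 in both | 0.181 | 64.7% | 64.5% | 5.2% |

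**Hand check of one row.** For a mean Spearman of 0.076, the t statistic is centred at 0.076 × √162/√(1 − 0.076²) = 0.97. The chance of exceeding ±1.97 is then about 16%, as simulated.

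**The case against.** The strongest reply is that the article nowhere states a pooled analysis and nowhere excludes arm. The covariate list is open: "by adjusting for pertinent covariates, such as BMI" gives an example, and the full protocol or a statistical analysis plan, neither shown, may name arm. A reader might infer that the authors decided to pool and to leave arm out; the text does not support that. What remains is that the first step, the plain Spearman correlation, carries no adjustment at all. Pooling is its natural reading, and the article names arm in the microbiome and sCCA analyses but not here.

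Second, the bias is conditional. A reader might infer that the changes are bound to correlate. They are not: with small shifts, or with markers that respond to different components, the error rate stays near 5%. The latter is plausible in a design meant to separate diet from weight loss.

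Third, the planning effects belong to bile acids only. Putting 1.2 SD on both variables in all three active arms gives about 76%, but that would need a very large metabolic or cytokine shift even in the Mediterranean-diet-alone arm, whose calorie target is weight maintenance. Nothing in the article supports that figure as an expectation.

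Fourth, BMI is not specified as baseline or change. Adjusting for change in BMI would remove part of the weight-loss effect, so the finding that BMI does not help holds for baseline BMI only.

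Finally, no significance level or decision rule is set for these correlations, and an unadjusted correlation is a legitimate description. That is why the remedy keeps it, as description.

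**Conclusion.** The point holds as a weakness in a supportive analysis. As written, the text permits a pooled change-on-change correlation in which arm can produce an association that does not exist within arms. The spurious correlation is modest, about 0.08 to 0.18 where both variables move by 0.67 SD or more in all three active arms. With 164 completers that is enough to raise the error rate from 5% to between 16% and about 65%. The range rests on the marker effects, normality and two-sided tests assumed above, and it falls back to about 5% under small or non-overlapping effects.

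A reader might go further and conclude that the primary analysis or the trial's whole mechanistic case is compromised. Neither follows. The primary outcomes are compared between arms, and those comparisons and the sample size are untouched. The mechanistic questions are also addressed by the microbiome models, regression, discriminant analysis, network modelling and sCCA.

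**What to change.** State that every correlation between a bile acid change and a marker change is a partial rank correlation that includes randomised arm as three indicator terms, alongside the other covariates. Base any inference on that result and label the unadjusted Spearman correlation as descriptive. Say also whether BMI means the baseline value or the change.

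The cost is three degrees of freedom out of about 160 and a sentence or two of text. No new data are needed, and the sample size does not change.
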